## Materials and methods

Method

This experimental study will be conducted in the Department of Prosthodontics, Sharad Pawar Dental College and Hospital, Sawangi (M), Wardha, India. The data will be collected in the postgraduate clinic of the Department of Prosthodontics. On the basis of the inclusion and exclusion criteria (Table 1), the patients will be divided randomly into two groups: Group A (n=20) (herbal denture adhesive without essential oil) and Group B (n=20) (herbal denture adhesive with essential oil). A total of 16 closed-ended questions will be asked of patients: eight during denture insertion without using denture adhesives and eight questions seven days after using denture adhesives.

**Table 1 TAB1:** Inclusion and exclusion criteria

Inclusion Criteria	Exclusion Criteria
Patients who are first-time denture wearers	Patients with tooth-supported overdentures
Patients who are old complete denture wearers	Patients with implant-supported overdentures
Patients who are willing to participate in the study	Patients with a single complete denture

The denture adhesive will be fabricated by utilizing carboxymethylcellulose with flavor, mineral oil, petroleum, silica particles, and mesoporous nanoparticles of the selected essential oil (cinnamon oil) with antimicrobial action incorporated into a gel for prolonged release, giving better effectiveness. In order to gather information about denture fitting, removal, chewing, retention, and phonetics, a standard questionnaire form will be given to each patient. Following the patient's answer to Questionnaire 1 (Table 2), a clinical examination and application of denture adhesive demonstration will take place, adhering to the guidelines provided by the manufacturer. The patients will be provided with an explanation of the cleaning routine and the administration of denture adhesive for the next seven days. The patients will be contacted back a week later to complete an additional questionnaire (Table 3) in which they will be asked to rate the denture's strength, biocompatibility, convenience, and masticatory abilities using the glue that was provided.

**Table 2 TAB2:** Questionnaire 1 (at the time of denture insertion) Reference: [1,6,7]

Sr. No.	Questions	Options	No. of Patients
1.	To what extent do you find the retention of your upper denture satisfactory?	Dissatisfied	
		Neutral	
		Satisfied	
2.	To what extent do you find the retention of your lower denture satisfactory?	Dissatisfied	
		Neutral	

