		Satisfied	
3.	To what extent do you find the chewing ability of your denture satisfactory?	Dissatisfied	
		Neutral	
		Satisfied	
4.	To what extent are you happy with the comfort of your new denture?	Dissatisfied	
		Neutral	
		Satisfied	
5.	To what extent do you find the speech and sound produced by the denture satisfactory?	Dissatisfied	
		Neutral	
		Satisfied	
6.	How satisfied are you with the way your dentures fit and removal?	Dissatisfied	
		Neutral	
		Satisfied	
7.	Does your denture harm the soft tissues in any way?	Yes	
		No	
8.	Do you have any issues with swallowing because of the denture?	Yes	
		No	

**Table 3 TAB3:** Questionnaire 2 (after seven days of denture insertion) Reference: [1,6,7]

Sr. No.	Questions	Options	No. of Patients
1.	To what extent are you satisfied with the adhesive's ability to keep your upper denture in place?	Dissatisfied	
		Neutral	
		Satisfied	
2.	To what extent are you satisfied with the adhesive's ability to keep your lower denture in place?	Dissatisfied	
		Neutral	
		Satisfied	
3.	How was your chewing experience after using this denture adhesive?	Worse	
		No difference	
		Better	
4.	For what duration did the denture adhesive work on your dentures?	≤4 hours	
		4-8 hours	
		8-12 hours	
5.	How does this denture adhesive taste?	Bad	
		Neither good nor bad	
		Good	
6.	How did you find it to remove the adhesive from your dentures?	Difficult	
		Neutral	
		Easy	
7.	How did you find it difficult to clean your denture after using the denture adhesive?	Difficult	
		Neutral	
		Easy	
8.	How difficult was it for you to wipe your oral cavity after using the denture adhesive?	Difficult	
		Neutral	
		Easy	

Sample Size

The sample size is determined using the following formula: n = {(Z 1-α/2 + Z 1-β)2 p1(1-p1) + p2 (1-p2)}/(p1-p2)^2^, where the proportion of outcome from group 1 (p1) = 0.37, the proportion of outcome from group 2 (p2) = 0.22, the level of significance (α) = 0.05, power (1-β) = 0.80, Z alpha value = 1.96, Z beta value = 0.84, and the total sample size = 40. The sample size estimation is done at a 95% confidence interval. Each group consists of 20 samples.

Statistical analysis

The statistical analysis will be done using IBM SPSS Statistics for Windows, Version 23 (Released 2015; IBM Corp., Armonk, New York). Descriptive statistics will be used for the mean distribution of both groups, and an independent sample t-test will be used for intergroup analysis between both groups.

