Age will be given using mean and standard deviation; however, frequency percentage will be used for qualitative characteristics. The independent t-test will be used to compare age between the two groups, and the Pearson chi-square test or Fisher's exact test will be used to compare all qualitative variables at a significant level of p-value ≤0.05 for all variables. The total of each questionnaire's scores will be used to determine the overall satisfaction with the results. Next, choose the percentage of satisfaction for every patient in both groups. The Wilcoxon signed-rank test will be used to compare patient satisfaction before and after the interview.

Ethical considerations

This study has been approved by the Institutional Ethics Committee of Datta Meghe Institute of Higher Education and Research (DMIHER(DU)/IEC/2024/56) dated May 11, 2024. Participant confidentiality will be maintained, and all procedures will adhere to ethical guidelines for research.

Trial registration

The study is registered with the Clinical Trial Registry-India under the CTRI Registration number CTRI/2024/06/068933, registered on June 14, 2024.

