## Results

The current study's findings will indicate that the application of herbal denture adhesive combined with essential oil will considerably improve the overall comfort of using the complete denture. It will reduce the bacterial growth and chances of mouth sores due to dentures. The expected results of the study indicate that the utilization of herbal denture adhesive combined with essential oil will increase the stability and retention of the dentures and the effectiveness of their retention over time.

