## Discussion

Denture adhesives are categorized based on how they are manufactured, such as powder, tapes, gels, and paste. Denture adhesive enhances retention, lessens denture soreness, avoids strangling the mucosal blood supply, and lessens the need for adjustments even when the denture fits.

A study by Mekkawy et al. involved 30 edentulous patients who were divided into two groups and given various types of denture adhesives (SECURE and COREGA) for seven days. The patients' satisfaction with denture retention, chewing ability, stability, and efficiency were assessed. The study found that the prosthetic denture adhesives significantly improved denture retention in the mandible and the duration of the adhesion in the mouth. However, there was no significant increase in the ability to remove the adhesive or maxillary denture retention. The study suggests that effective use of denture adhesives requires patient education and proper dental guidance [1].

A study by Yadav et al. involved 30 edentulous patients with resorbed ridges. They used isabgol, fixon powder, and Fittydent powder denture adhesives. Incisal bite force and retention force were measured using FlexiForce sensors (Tekscan, Massachusetts) and digital force gauges. Fittydent powder and isabgol significantly increased retention and biting force compared to fixon [4].

A study by Koronis et al. involved 30 edentulous patients who had their denture-supporting tissues and old dentures renewed. They were prescribed three different brands of denture adhesives: Fittydent, Seabond, and Protefix. The adhesives were used for 48 hours on the lower denture, with participants spending 24 hours without adhesives. The results showed that denture adhesives generally enhance patient satisfaction and chewing ability, especially in those with poor Kapur index and poor denture retention. Fittydent was found to be the most effective adhesive [8].

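### The only question on how long the adhesive holds (Table 3, item 4) has answer bands that overlap at 8 hours, arguably also at 4, and no band above 12 hours: a minor form defect that is cheap to correct before first use

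*Protocol article*

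**What the plan says.** All questions on both forms are closed-ended: "A total of 16 closed-ended questions will be asked of patients" (Materials and methods, Method). Item 4 of Table 3 reads "For what duration did the denture adhesive work on your dentures" and has three answers: ≤4 hours, 4-8 hours, 8-12 hours. The article gives no rule for an answer on a boundary and no open answer. No other item in Table 2 or Table 3 asks about duration.

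Under Statistical analysis the item has two possible uses. As a categorical item it falls under "the Pearson chi-square test or Fisher's exact test will be used to compare all qualitative variables". As part of Questionnaire 2 it enters the sum: "The total of each questionnaire's scores will be used to determine the overall satisfaction with the results".

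Two other places touch on duration. The Results section expects that the essential-oil adhesive "will increase the stability and retention of the dentures and the effectiveness of their retention over time". The Discussion reports that, in a cited comparison of two other adhesives, the products "significantly improved denture retention in the mandible and the duration of the adhesion in the mouth". Neither gives hours.

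**The concern.** A closed question needs exactly one box for every possible answer, and this one fails in two ways. At a shared boundary the patient picks between two valid boxes, so equal hold times can be recorded differently. Above 12 hours no box applies, so the patient ticks 8-12 hours or leaves the item blank. Ticking the top box merges long holds with moderate ones; leaving it blank removes the longest holds.

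At stake is the A versus B comparison on duration, the one outcome that speaks directly to the Results section's expectation about retention over time. If one adhesive holds well past 12 hours in many patients, the form hides part of that advantage. The questionnaire total is affected too, but only through one item in eight.

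**Working it through.** **Plan's own figures.** The article gives no hold times, so it has no figure on this point to reproduce. Its one computed figure, the sample size, is a separate matter: the stated inputs give (1.96 + 0.84)² × (0.37×0.63 + 0.22×0.78) / 0.15² = 7.84 × 0.4047 / 0.0225 ≈ 141 per group, not 20. Only the planned 20 per group is used below.

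**Step 1: fit of whole-hour answers to the printed bands.**

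| Reported hold (hours) | Boxes that fit |
|---|---|
| 1 to 3 | one |
| 4 | two (≤4 and 4-8) |
| 5 to 7 | one |
| 8 | two (4-8 and 8-12) |
| 9 to 12 | one |
| 13 or more | none |

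At 4 hours the ≤ sign gives the patient some guidance; at 8 hours there is none.

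**Step 2: what each fault could cost.** Assumptions, none from the article: hold times are normal, limited to 0.5 to 24 hours and rounded to the hour; 20 per group; answers above 12 hours go into the top box; two-sided Mann-Whitney test at 0.05; 4000 simulated trials per row. The Monte Carlo standard error is at most √(0.25/4000) ≈ 0.8 points. SD is 3 hours and Group B holds 2 hours longer.

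| Mean A / B (h) | Group B above 12 h | All answers at 4 or 8 h | Power: printed, boundary answers at random | Power: three clean bands | Power: four clean bands |
|---|---|---|---|---|---|
| 6 / 8 | 6.7% | 20.0% | 44.8% | 45.6% | 46.8% |
| 8 / 10 | 20.1% | 15.7% | 37.0% | 40.2% | 46.0% |
| 10 / 12 | 43.5% | 9.1% | 26.2% | 29.8% | 44.9% |
| 12 / 14 | 69.2% | 3.9% | 7.2% | 12.1% | 41.1% |

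- Loss from the overlap (clean three minus printed): 0.8, 3.2, 3.6 and 4.9 points. Over a wider set of assumed means and SDs it is about 0 to 7.
- Loss from the missing top band (four minus clean three): 1.2, 5.8, 15.1 and 29.0 points.
- Total: 2.0, 9.0, 18.7 and 33.9 points.

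**Step 3: does the repair work under the planned test?** Same approach with larger differences, printed form v four bands (2000 trials for chi-square; standard error at most √(0.25/2000) ≈ 1.1 points).

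| Mean A / B, SD (h) | Mann-Whitney | Pearson chi-square |
|---|---|---|
| 5 / 7, SD 3 | 42% v 43% | 35% v 30% |
| 6 / 9, SD 4 | 53% v 58% | 44% v 39% |
| 8 / 11, SD 4 | 45% v 56% | 35% v 39% |
| 9 / 12, SD 4 | 40% v 57% | 28% v 37% |
| 10 / 14, SD 4 | 51% v 77% | 36% v 59% |
| 10 / 13, SD 3 | 46% v 78% | 35% v 61% |

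With an ordered test the fourth band does not lose power in any row. With Pearson chi-square, which ignores the order and spends an extra degree of freedom, it costs about 5 points when holds are short.

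**The case against.** The strongest reply is that the consequences are small or hypothetical, and much of it stands.

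- **Prolonged release.** A reader might infer from "incorporated into a gel for prolonged release, giving better effectiveness" that Group B is designed to hold longer. In context the phrase describes the cinnamon oil with its antimicrobial action; it makes no claim about adhesion time.
- **A cap where the benefit must lie.** A reader might also infer that the form cuts off the very range in which Group B is expected to win. The Results section expects more lasting retention but gives no hours, and the cited study concerned other products. A better Group B could fall wholly within the printed bands.
- **A measure misclassified as a whole.** Only answers at the boundaries are ambiguous. The ambiguity follows the same rule in both arms, so it is noise and not built-in bias. A patient above 12 hours who ticks the top box is still ranked longest, which is coarsening and not a wrong answer.
- **A peripheral item.** The Introduction states the aim as patient satisfaction with retention, and items 1 and 2 of Table 3 ask that directly.
- **The planned test.** The largest gains come from a rank test that the article does not assign to this item, and from assumed Group B means above 12 hours.

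What the reply does not remove is the fault on the form. The article does not exclude holds above 12 hours, and no later analysis can separate answers that the form has merged.

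**Conclusion.** The point holds as a minor defect. Item 4's bands overlap at 8 hours, and arguably at 4, and stop at 12, on the only item about duration.

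The overlap is worth about 0 to 7 points of rank-test power. The cost of the missing top band depends on how many patients exceed 12 hours. Taken together, the loss runs from about 1 point (5 v 7 hours, SD 3) to about 34 points (12 v 14 hours, SD 3). That whole range rests on assumed hold times, and the article offers no basis for choosing a value within it. Any effect of the cap would be towards no difference. The article does not support the conclusion that the trial's main comparison is biased.

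**What to change.** Before the form is first used, print item 4 with four options: ≤4 hours, >4 to 8 hours, >8 to 12 hours, >12 hours. Every answer then has exactly one box.

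Pair this with an ordered comparison between groups for the item, either Mann-Whitney or a linear-by-linear trend test, in place of Pearson chi-square. Without that, the extra level can reduce power when holds are short.

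Keep the item's weight in the questionnaire total unchanged. The article does not give the scoring. If, for illustration, each of the eight three-option items scored 0 to 2, a fourth level scored 3 would raise the item's share of the maximum from 2/16 = 12.5% to 3/17 = 17.6%. Either merge the top two bands for the total only, or rescale the item to its former range, and state which in advance.

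The cost is an edit to one item on the form, a sentence in the analysis section and a minor notification to the ethics committee. No extra patients or visits are needed. The downside is a small departure from the source questionnaires.

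### The 80% power is claimed for an unnamed yes/no outcome (0.37 versus 0.22) tied to no specific test, and it holds for no analysis the plan describes

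*Protocol article*

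**What the plan says.** Protocol article, Materials and methods, Sample Size: the formula is the one for comparing two independent proportions. Its inputs are "the proportion of outcome from group 1 (p1) = 0.37, the proportion of outcome from group 2 (p2) = 0.22", with "the level of significance (α) = 0.05, power (1-β) = 0.80" and "Z alpha value = 1.96, Z beta value = 0.84". The result is given as "the total sample size = 40", split into two groups of 20. The section does not say what the outcome is, what counts as having it, or whether group 1 is Group A or Group B.

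Protocol article, Materials and methods, Statistical analysis, describes four things:

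- For the comparison of groups, "an independent sample t-test will be used for intergroup analysis between both groups". No variable is named in that sentence. The one variable explicitly assigned to a t-test elsewhere in the section is age.
- For overall satisfaction, "The total of each questionnaire's scores will be used to determine the overall satisfaction with the results", followed by "Next, choose the percentage of satisfaction for every patient in both groups".
- A Wilcoxon signed-rank test compares satisfaction before and after.
- Chi-square or Fisher's exact tests compare all qualitative variables, at p ≤ 0.05.

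All eight items in Table 3, answered after adhesive use, have three response options. The only yes/no items are items 7 and 8 of Table 2, which are answered before any adhesive is applied.

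**The concern.** A power statement means something only for a stated outcome, a stated difference and a stated test. Here the outcome behind 0.37 and 0.22 is missing, and the analysis text turns to a score total, a per-patient percentage and a t-test. No cut-point turns a day-7 item or the total into the yes/no outcome used for sizing.

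The reader is told that the trial has an 80% chance of detecting its planned difference. If that figure belongs to none of the tests to be run, a null result would be taken as more informative than it is. A positive result on the total could not be set against any difference planned in advance.

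**Working it through.** **Inputs, all from the Sample Size section.** p1 = 0.37, p2 = 0.22, difference 0.15; Z values 1.96 (two-sided 0.05) and 0.84 (80% power); 20 per group.

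**1. The plan's own figure.** Standard two-proportion formula, with the Z term multiplying both variances:

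- p1(1 − p1) = 0.37 × 0.63 = 0.2331
- p2(1 − p2) = 0.22 × 0.78 = 0.1716
- sum = 0.4047
- (1.96 + 0.84)² = 7.84
- n = 7.84 × 0.4047 / 0.15² = 3.1728 / 0.0225 = 141.02, so 142 per group and 284 in total

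Read exactly as printed, with the Z term multiplying only the first variance: (7.84 × 0.2331 + 0.1716) / 0.0225 = 88.8, so 89 per group. The pooled-variance version gives 144 per group, or 157 with continuity correction. One-sided versions give 112 to 127 per group. None gives 20 per group, or 40 per group.

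**2. If the sized outcome is one of the qualitative variables tested by chi-square or Fisher.** Power at 20 per group for 0.37 versus 0.22, two-sided 0.05:

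- Normal approximation: the mean proportion is 0.295. The null standard error is √(2 × 0.295 × 0.705 / 20) = 0.1442, and the alternative standard error is √(0.4047 / 20) = 0.1423. Power = Φ[(0.15 − 1.96 × 0.1442) / 0.1423] = Φ(−0.93), about 17.6%.
- Exact enumeration of all 2 × 2 tables, rejecting at p ≤ 0.05: 18.6% for the uncorrected chi-square test and 11.2% for Fisher's exact test.
- If 40 is read as the size of each group, the normal approximation still gives only 31.0%.

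**3. If the between-group test is a t-test on the total score.** The article gives no mean difference and no SD for the total, so only a standardised difference can be stated. With 20 per group and two-sided 0.05, the normal approximation for 80% power is (1.96 + 0.84) × √(2/20) = 0.89 SD. The t-distribution calculation gives 0.909 SD. Under assumed true differences of 0.3, 0.5 and 0.8 SD, power is about 15%, 34% and 69%.

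**4. If it is the Wilcoxon signed-rank test.** This is a paired before/after comparison. A formula for two independent proportions does not describe it, and no before/after effect is stated.

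| Planned analysis | Linked to 0.37/0.22 in the text? | What 20 per group gives |
|---|---|---|
| Chi-square or Fisher on a qualitative item | No item named | About 11-19% power at those rates |
| t-test between groups | No; variable not named | 80% only at 0.91 SD |
| Wilcoxon before/after | No | Not covered by the formula |

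**The case against.** The strongest reply is that the plan does contain tests of the kind that was sized. All qualitative variables are to be compared by chi-square or Fisher's exact test, and Tables 2 and 3 have a column for the number of patients giving each response. A reader might infer that the yes/no outcome is analysed nowhere; the article does not support that, because a comparison of item proportions is planned in general terms. What is missing is any link from 0.37 and 0.22 to a particular item and cut-point. The reply also does not rescue the power, which is 11-19% for exactly that test.

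A second reply is that the t-test is not stated to be on the total. That is correct: treating the total as the t-test variable is a plausible reading and not the text. The point does not depend on it, since 80% power is not established under either reading.

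A third is that the full protocol may name the outcome, because an article condenses. It may. But the article itself prints the formula, the inputs, the sample size and the tests, and these do not fit together.

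Three further inferences are tempting and should not be drawn:

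- That p1 = 0.37 and p2 = 0.22 plan for the essential-oil group to do worse, or better. Neither the outcome nor the group labels are given. The formula is symmetric in p1 and p2, so direction changes neither n nor power. It is a consequence of the unnamed outcome, not a second defect.
- That 37% versus 22% can be converted into a power for the total score. This would need assumed response splits, item scores and correlations between items, and the article gives none.
- That 40 came from a one-sample precision formula (1.96² × 0.37 × 0.63 / 0.15² = 39.8). The match may be chance. That formula is not the one printed, and it carries no power.

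**Conclusion.** The concern holds in this form: the stated 80% power rests on an outcome that is not named, dichotomised or tied to a group label or specific test, and it applies to none of the analyses described. At the stated rates with 20 per group, a two-proportion test has about 11% (Fisher) to 19% (uncorrected chi-square) power, and about 142 per group would be needed for 80%. A t-test reaches 80% only for a difference of 0.91 SD, an effect the plan does not state.

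The two-proportion figures rest on the article's own inputs, two-sided testing at 0.05 and no loss of patients. The t-test figure assumes a continuous, roughly normal score with equal variances. It cannot be turned into score points, because no SD is given.

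**What to change.** Use one endpoint for both sizing and analysis, and restate its power at 20 per group. Either of two routes will do:

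- **(a) Keep the proportions.** Name the yes/no outcome behind 0.37 and 0.22, including the item, the time point and which responses count. State which adhesive group is group 1. Make the difference in proportions, with its confidence interval, the lead analysis. Replace the 80% with the power that applies: about 11% for Fisher's exact test or about 19% for the uncorrected chi-square test.
- **(b) Use the score.** Name the day-7 total, compared between groups by t-test, as the lead endpoint. Replace the two-proportion statement with: 20 per group gives 80% power for a difference of 0.91 SD (two-sided 0.05). This describes what the fixed sample size can detect; it does not show that such a difference is likely.

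If 40 patients are kept, either route costs only a rewording of the Sample Size and Statistical analysis sections, with no new data. The downside is that the stated power becomes less favourable. Keeping 80% power for 0.37 versus 0.22 is not a wording change: it would need 284 patients, 244 more than planned (284 − 40).

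### The stated total of 40 does not follow from the printed formula and inputs, which require about 142 per group; 20 per group gives about 18% power, not 80%

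*Protocol article*

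**What the plan says.** Under Materials and methods, Sample Size, the protocol article prints the formula "n = {(Z 1-α/2 + Z 1-β)2 p1(1-p1) + p2 (1-p2)}/(p1-p2)^2" and supplies every input: "the proportion of outcome from group 1 (p1) = 0.37, the proportion of outcome from group 2 (p2) = 0.22", "the level of significance (α) = 0.05", power of 0.80, and "Z alpha value = 1.96, Z beta value = 0.84, and the total sample size = 40". The paragraph closes with "Each group consists of 20 samples". The Abstract and the Method paragraph repeat 20 per group.

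No other basis for 40 is given: no mean and standard deviation, no paired effect, no dropout allowance and no statement about feasibility. The paragraph does not say which question or response the two proportions describe. The Statistical analysis section names the Pearson chi-square or Fisher's exact test for comparing qualitative variables.

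**The concern.** A difference of 15 percentage points between rates in this range normally needs well over 100 patients per group, so a result of 20 per group suggests an arithmetic error or a wrong input.

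The study's aim is to compare the two adhesives, and this calculation is the only justification for its size. If the power claim is false, a non-significant result may be read as showing no difference when the trial had little chance of detecting the planned one. If the true difference is near 15 points, a significant result would tend to overstate it, because only a much larger observed difference is likely to reach significance with 20 per group.

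**Working it through.** **Inputs**, all from the Sample Size paragraph: p1 = 0.37; p2 = 0.22; Z values 1.96 and 0.84; stated n = 20 per group.

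**Attempt to reproduce the stated figure.** The standard form of the formula is

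n per group = (Z₁₋α/2 + Z₁₋β)² × [p1(1−p1) + p2(1−p2)] / (p1−p2)²

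- (1.96 + 0.84)² = 7.84
- p1(1−p1) + p2(1−p2) = 0.2331 + 0.1716 = 0.4047
- (p1−p2)² = 0.15² = 0.0225
- n = 7.84 × 0.4047 / 0.0225 = 141.02, so 142 per group and 284 in total

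The stated 20 per group is not reproduced.

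**Other readings of the same inputs**

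| Reading | n per group |
|---|---|
| Brackets taken literally: (7.84 × 0.2331 + 0.1716) / 0.0225 | 88.85, so 89 |
| Pooled variance, two-sided | 144 |
| Pooled, with continuity correction | 157 |
| Arcsine | 143 |
| Unpooled, one-sided | 112 |
| Pooled, one-sided | 114 |
| One-sample version | 66 to 75 |

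None gives 20 per group or 40 in total. Values near 20 appear only if the formula or an input is altered:

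- Z factor omitted: 0.4047 / 0.0225 = 17.99
- denominator not squared: 7.84 × 0.4047 / 0.15 = 21.15
- one proportion replaced by its complement (0.37 versus 0.78, or 0.63 versus 0.22): 7.84 × 0.4047 / 0.41² = 18.87

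**Power at 20 per group for 0.37 versus 0.22**

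- Standard error = √(0.4047 / 20) = 0.1422
- 0.15 / 0.1422 − 1.96 = −0.905, giving power of 18.3%
- Pooled-variance version: 17.6%
- Exact enumeration of both binomials: 18.6% for the uncorrected Pearson chi-square test, 11.2% for Fisher's exact test

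**Precision.** The 95% confidence interval half-width is 1.96 × 0.1422 = 0.279, about 28 points, against an assumed difference of 15.

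**Overestimation.** In the same enumeration, the chi-square-significant results have a mean absolute observed difference of about 35 points when the true difference is 15.

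**What 20 per group can detect.** From a 22% base, 80% power needs a rate in the other group of about:

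- 62% by the formula: 7.84 × (0.62 × 0.38 + 0.1716) / 0.40² = 19.95
- 66% by exact chi-square
- 70% by exact Fisher

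These are differences of 40, 44 and 48 points.

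**The case against.** The strongest reply is that the document shows only that the inputs and the sample size disagree, not which is wrong. If one proportion was printed as its complement, the formula gives 19 per group, and at 20 per group power would be about 82% (0.41 / 0.1422 − 1.96 = 0.92). This is conjecture, but it is a good reason to trace the source of 0.37 and 0.22 before rewriting the paragraph. It does not rescue the text as printed.

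Other points have some weight:

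- **Formula layout.** The lost superscript and bracket may come from text extraction. The finding does not depend on them, since both the standard and the literal reading miss 20 by a wide margin.
- **Other analyses.** A t-test between groups and summed questionnaire scores are also planned, and their power does not follow from 0.37 and 0.22. That is true, so the power figures here apply to a single yes/no outcome. But the paragraph bases the size on two proportions and nothing else.
- **Acknowledged limitation.** The Study limitation paragraph says that sample size limits generalizability. It does not withdraw the 80% power claim.
- **Direction.** If the outcome is satisfaction and groups 1 and 2 are A and B, the inputs assume that the essential-oil adhesive does worse, against the expected results. The article fixes neither condition, so this shows only why the outcome must be named. The calculation is two-sided, so n is unaffected.
- **Reason for 40, and the exploratory label.** No feasibility basis is documented, so it should be stated only if true. Whether to call the comparison exploratory is a matter of judgement, since comparing the adhesives is the stated aim.

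**Conclusion.** The concern holds. With the printed inputs the required size is 142 per group (284 in total), and the stated 40 is about one seventh of that. Power at 20 per group is about 18% by the formula or the chi-square test and about 11% by Fisher's exact test, so the 80% claim overstates power more than fourfold.

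This rests on the printed rates being the intended ones, on a two-sided 5% test (Z = 1.96), on equal groups and on no dropout; any loss of patients would lower power further. The detectable differences of 40 to 48 points assume a 22% base rate. The paragraph must be corrected, because it is the only justification for the size of the trial.

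**What to change.** 1. Trace the source of 0.37 and 0.22, and name the questionnaire item, the response and the group to which each refers. If an input was misprinted, correct it and rerun the calculation.
2. If the rates stand and 20 per group is kept, delete the 80% power statement. Give the actual reason for 40 patients (feasibility, if that was the reason). State that power for 37% versus 22% is about 11% to 19% depending on the test, and that the smallest difference detectable with 80% power from a 22% base is about 40 to 48 points.
3. Print the formula with full brackets: n per group = (Z₁₋α/2 + Z₁₋β)² [p1(1−p1) + p2(1−p2)] / (p1−p2)².
4. Report the comparison of Group A with Group B as an estimated difference with a 95% confidence interval, preferably labelled exploratory, and do not read a non-significant result as evidence of no difference.

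The cost is a rewrite of one paragraph and a less favourable stated power. No extra patients are needed.
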